## 2. Methods

### 2.1. Study design

This will be a multi-center, randomized, double-blind, placebo-parallel controlled trial. Between January 2020 and December 2023 in 9 centers including The First Affiliated Hospital of Guangzhou University of Traditional Chinese Medicine, the Affiliated Hospital of Liaoning University of Traditional Chinese Medicine, Yueyang Integrated Hospital of Traditional Chinese and Western Medicine Affiliated to Shanghai University of Traditional Chinese Medicine, the First Affiliated Hospital of Guangxi University of Traditional Chinese Medicine, Hainan Hospital of Traditional Chinese Medicine, Maoming Hospital of Traditional Chinese Medicine, Dongguan People’s Hospital, the Second Affiliated Hospital of Guangzhou Medical University, and Beihai People’s Hospital, a total of 300 patients diagnosed with AMI and undergoing PCI within 12 hours of diagnosis, with the Chinese medicine diagnosis of “Qi-Yin deficiency and blood stasis,” will be randomly divided into 2 groups: the control group that will be administered conventional Western medicine plus placebo, and the experimental group that will be administered CXSTC along with the conventional Western medicine. Figure 1 shows a flow chart of the study. Figure 2 presents the schedule of enrollment, interventions, and assessments.

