### 2.4. Sample size

Taking α = 0.05 and β = 0.15, a 2-sided test will be used. The estimated sample incidence of P_1_ = 25% for the test group and P_2_ = 43% for the control group will be brought into the following equation:

$$\begin{array}{l} n_{1}=n_{2}=1641.6\times {\left(\frac{u_{\alpha }+u_{2\beta }}{sin^{-1}\sqrt{P_{1}}-sin^{-1}\sqrt{P_{2}}}\right)}^{2} \end{array}$$

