### 2.5. Randomization and blinding

The randomization scheme provided by the Department of Statistics, Guangzhou University of Traditional Chinese Medicine. A stratified randomization method will be used. Statistical analysis system software will be applied to generate a randomized allocation of the treatments received by the patients, that is, the treatment assignments corresponding to the running numbers 001 to 300 will be listed, and the study subjects will be randomly divided into 2 groups: the test group and the control group.

The study will have a double-blind design with placebo as the control, and the number of cases in the test and control groups will be 1:1, which will be a secondary blinding done by the Statistics Department of Guangzhou University of Traditional Chinese Medicine. The trial drug and placebo will be provided by Guangdong Zhongsheng Pharmaceutical Co., Ltd. and packaged according to the random assignment and blinding methods. The blind codes will be sealed in duplicate and separately stored in the drug clinical trial institution and the sponsoring unit in charge of this study.

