### 2.7. Outcomes

#### 2.7.1. Efficacy indicators

(1) The main efficacy indicator will be the incidence of HF. The incidence of HF was recorded on days 3, 7, 14, 1 month, and 3 months after drug administration, and after discontinuation of the drug until 3 months.(2) Secondary efficacy indicators

① Cardiac function classification: before treatment and after drug administration on days 3, 7, 14, 1 month, and 3 months and after discontinuation of the drug until the 3rd month of the examination record.

② Cardiac ultrasound: the examination records shall be recorded before treatment and on days 7 and 3 months after drug administration.

③ Six-minute walk test score: recorded on days 7, 14, 1 month, and 3 months after drug administration.

④ TCM syndrome score: recorded before treatment and on days 7, 14, 1 month, and 3 months after drug administration. The efficacy = (the integral value before treatment − the integral value after treatment)/ the integral value before treatment × 100%); It is assessed at 4 levels: clinical recovery: clinical symptoms or syndrome score decreased by ≥95% from the baseline; marked efficacy: the syndrome score decreased by ≥70% and <95%; efficacy: the syndrome score was a decrease of at least 30% and <70%; invalid: the syndrome score was a decrease of <30%; and worsen: the syndrome score exceeded the baseline after treatment.

⑤ Quality of survival score (the Minnesota living with heart failure questionnaire): recorded before treatment and on days 14, 1 month, and 3 months after drug administration.

⑥ Brain natriuretic peptide level was recorded before treatment and on days 3, 7, 14, and 3 months after drug administration.

⑦ Ultrasensitive C-reactive protein level: recorded before treatment and on days 3, 7, 14, and 3 months after drug administration.

Total efficacy rate = (clinical recovery + marked efficacy + efficacy) cases/a total number of cases × 100%.

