### 2.9. Statistical analysis plan

All data will be statistically analyzed using SPSS 23.0 software. The measurement data will be expressed as mean ± standard deviation to test the normality of the samples. If the distribution is normal and the variances are homogeneous, the *t* test shall be used. The rank sum test will be used if the distribution is not normal or the variances are not equal. Count data will be expressed as percentages and tested by the χ^2^ test or Fisher method. Rank data will be tested by rank sum test; the Cox regression model will be used to observe the relationship between the risk of occurrence of endpoint events and each influencing factor. A 2-sided *P* value < .05 will be set as the significant level.

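### Randomisation is stratified but the stated test of the primary endpoint is not; if the strata predict heart failure, the test is conservative and slightly inefficient

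*Protocol article*

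**What the plan says.** All references are to the protocol article.

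- **Allocation (section 2.5):** "A stratified randomization method will be used". The factors are not named. The same section describes a list in which "the treatment assignments corresponding to the running numbers 001 to 300 will be listed".
- **Setting (section 2.1):** recruitment runs "Between January 2020 and December 2023 in 9 centers", so centre is a plausible stratification factor, but the article does not say that it is one.
- **Primary endpoint (section 2.7.1):** "The main efficacy indicator will be the incidence of HF", a yes/no outcome for each patient.
- **Test (section 2.9):** "Count data will be expressed as percentages and tested by the" chi-square test or the Fisher method. Strata are not mentioned.
- **Model (section 2.9):** "the Cox regression model will be used to observe the relationship between the risk of occurrence of endpoint events and each influencing factor". The section does not say whether the stratification factors are among these, and does not call this model the primary analysis.
- **Design assumptions (section 2.4):** "Taking α = 0.05 and β = 0.15, a 2-sided test will be used", with "P_1_ = 25% for the test group and P_2_ = 43% for the control group".

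**The concern.** Balancing treatment within strata removes differences between strata from the treatment comparison. A pooled chi-square test does not know this. It computes its variance as if the two arms were simple random samples, so variation between strata still counts as error. When HF risk differs between strata, the standard error is too large, the true rejection rate under the null falls below the nominal 5%, and some of the precision that stratification provides goes unused.

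The direction is safe, because a false positive becomes less likely. What is at stake is calibration and efficiency. Section 3 itself lists the small number of cases as a limitation, so precision that costs nothing is worth keeping.

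**Working it through.** **1. The plan's own figure.** The arcsine formula in section 2.4, in degrees, with arcsin√0.25 = 30.00, arcsin√0.43 = 40.98 and normal quantiles 1.960 and 1.036, gives

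n = 1641.6 × [(1.960 + 1.036) / (30.00 − 40.98)]² ≈ 122.3, so 123 per arm and 246 in total.

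Unstratified power is 85.1% at 123 per arm and 91.2% at 150 per arm (the stated 300). The gap between 246 and 300 is a separate matter. Here it shows only that an unstratified test at N = 300 starts above the planned 85%. The design odds ratio is (0.25/0.75) / (0.43/0.57) = 0.44.

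**2. Size of the unstratified test, in closed form.** Take K equal strata with 1:1 allocation in each, stratum HF rates with mean p̄ and variance V, and no treatment effect, with n patients per arm.

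- True variance of the difference: (2/n) × [p̄(1 − p̄) − V].
- Variance used by the chi-square test: (2/n) × p̄(1 − p̄).
- Ratio: R = 1 − V / [p̄(1 − p̄)].
- Actual rejection rate at nominal 5%: 2 × [1 − Φ(1.96/√R)].

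The documents give no between-stratum variation, so a range is assumed. For nine evenly spaced centre rates, V = step² × (81 − 1)/12.

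- Rates 10% to 62%: step 0.065, V = 0.0282, p̄ = 0.36, R = 1 − 0.0282/0.2304 = 0.878, 1.96/√R = 2.09, rejection 3.6%.
- Rates 20% to 48%: step 0.035, V = 0.0082, p̄ = 0.34, R = 1 − 0.0082/0.2244 = 0.964, 1.96/√R = 2.00, rejection 4.6%.
- Equal rates: V = 0, R = 1, rejection 5.0%.

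**3. Simulation, centre as stratum** (nine centres, 17 per arm in each, so 306 patients, the nearest equal split to 300). The null columns use the centre rates shown. The power columns use overall rates of 25% v 43%.

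| Centre HF rates | Null: chi-square | Null: CMH | Power: chi-square | Power: CMH |
|---|---|---|---|---|
| 10% to 62% | 3.7% | 5.0% | 93.0% | 94.6% |
| 20% to 48% | 4.6–4.9% | 4.9–5.2% | 92.2% | 92.7% |
| all equal | about 5% | about 5% | 91.8% | 91.7% |

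The simulation agrees with the closed form. The range in the second row is the spread between separate runs.

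**4. Wider range of stratum strength** (40,000 trials per cell, two or nine equal strata, null rate 34%, SD of the log-odds of HF between strata as shown; power at N = 300 and 25% v 43%).

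| SD | Null: chi-square | Null: CMH | Power: chi-square | Power: CMH |
|---|---|---|---|---|
| 0 | 5.0% | 4.9–5.0% | 91% | 91% |
| 0.5 | 4.4% | 4.8–5.1% | 92–93% | 93% |
| 1.0 | 2.9–3.3% | 5.0–5.1% | 93–94% | 95–96% |
| 1.5 | 1.7–2.0% | 4.8–4.9% | 95–96% | 98% |

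The largest gain at N = 300 is 98.1% − 94.7% = 3.4 points (two strata, SD 1.5). With overall rates held at 25% and 43%, chi-square power does not fall as the strata become more prognostic, because balanced allocation reduces the true variance. The loss is only relative to CMH. At N = 246 the gain is 0 to 5.6 points and chi-square power is still 85% or more.

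**The case against.** **Section 2.9 is a short summary in an article, and a fuller analysis plan may adjust for the strata.** This stands in part. Unnamed factors, and how the 001 to 300 list is divided by stratum, are details that an article may leave to the full documents; neither is held against the plan here. But section 2.9 does more than stay silent. It names a test for binary outcomes, and that test is unstratified. A later stratified analysis would depart from the published text, so the two should be reconciled before unblinding.

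**The Cox model could contain the strata.** It could, and a reader should not infer that they are excluded. But it is not designated as the primary analysis, and the strata are not named in it.

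**The patients are alike.** Sections 2.3.5 and 2.3.6 require an ejection fraction above 50%, exclude Killip II or above and exclude previous heart failure or old infarction. A range of 10% to 62% across centres may therefore be too wide. This stands: the milder scenario may be nearer the truth, and there the effect is small.

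**Stronger readings that the documents do not support.**

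- That the 5% test is certainly not a 5% test. This depends on prognostic strata, which the article does not establish.
- That about 8 points of power are lost. Simulated power of 55% v 63% arises with an odds ratio of 0.55 and rates of 10% to 62%. The design's odds ratio is 0.44, and there the gain is 0 to 1.5 points over the centre scenarios.
- That the confidence interval is too wide. No interval for the primary comparison is described.
- That Fisher's conservatism belongs to this point. It comes from the discreteness of that test, not from ignoring strata.

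**Conclusion.** The point holds as a mismatch between stated design and stated analysis, with a conditional and modest effect. If the stratification factors predict HF, the unstratified test is conservative: about 3.7% with centre rates of 10% to 62%, near 5% with 20% to 48%, and as low as about 1.7% with very strong strata. At 25% v 43% and about 300 patients, a stratified test gains about 0 to 1.5 points of power, up to about 3 with stronger strata, and power stays above 85% either way. If the factors do not predict HF, nothing is lost. Type I error is not inflated, so the validity of a positive result is not in question.

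These sizes rest on assumptions that the documents do not supply: centre as the stratum, equal stratum sizes, exact balance within strata, and the assumed spread of HF rates. The mismatch itself rests only on sections 2.5 and 2.9.

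**What to change.** In section 2.9, state that HF incidence will be compared by a CMH test stratified by the randomisation factors, or by logistic regression adjusted for them, in place of the plain chi-square or Fisher test. Name those factors there. Stratify the Cox model by the same factors. Set a rule for pooling sparse strata before unblinding; if centre is a factor, nine centres share 300 patients and some strata may be small.

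The cost is a few lines of analysis wording. Sample size, data collection and allocation are unchanged. In the simulations CMH kept its level at about 5%, and where the strata were not prognostic its power equalled that of chi-square within simulation error.

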## 3. Discussion

In the present study, patients with AMI will be studied, and early intervention with the classical Chinese medicine CXSTC will be combined with modern standardized medical therapy. It is hypothesized that CXSTC will further improve the development of ventricular remodeling and HF after AMI. A multi-center, randomized, double-blind, placebo-controlled clinical study shall be conducted using the incidence of HF as the primary efficacy index and ventricular remodeling, TCM syndrome score, quality of survival score, and the incidence of major adverse cardiovascular events as secondary indices.

Thus far, there is no standard large sample of clinical trials to evaluate the clinical studies of CXSTC for the prophylactic treatment of patients with post-infarction HF. Through this clinical study, we hope to provide a clinical evidence-based basis for Chinese medicine prevention and treatment for post-infarction HF. However, we also need to recognize the limitations of this trial. The small number of cases makes it difficult to make a case for the clinical efficacy of CXSTC for the prevention of post-infarction HF. Second, post-infarction ventricular remodeling is a chronic process, and although the patients included in this study will be closely monitored in the short term, it is still difficult to determine the long-term prognosis of the patients with a follow-up period of up to 6 months. Finally, the efficacy and safety of TCM in combination with western drugs need to be further investigated. We hope that further studies will be conducted in the future to provide a clinical evidence base for the use of TCM in the prophylactic treatment of post-infarction HF.
